**Revision History**

| Version 1  Version 2 | Date 12.31.20  Date 4.20.21 |
| --- | --- |

# Abstract

| Title | Randomized trial of a contingency management smoking cessation intervention for homeless adults |
| --- | --- |
| Study Description | In this pilot randomized controlled trial (RCT), we will (1) adapt a known-efficacious extended CM cessation intervention to a novel population and setting, with the ultimate goal of increasing long-term abstinence among homeless adults seeking care in safety net health clinics, (2) develop a corresponding RCT protocol, and (3) conduct a pilot RCT to assess the feasibility and acceptability of the RCT. If the pilot RCT is feasible and acceptable, we will test the adapted intervention in a subsequently-funded, full-scale randomized controlled trial. |
| Study Intervention | In this study, we will test a contingency management intervention for carbon monoxide-verified smoking abstinence for people experiencing homelessness. |
| Study Population | The proposed study aims to enroll 90 homeless participants who are representative of the racial/ethnic and gender diversity of the homeless population in San Francisco. There are no exclusion criteria for this study based on gender, race, or ethnicity. We estimated our targeted enrollment based on the point-in-time count of the homeless population that occurred in 2010 in San Francisco. In 2019, there were 7499 unsheltered or publicly sheltered homeless persons in San Francisco, of whom 29% were white, 37% were black, 5% were American Indian/Alaskan Native, 5% were Asian, 2% were Native Hawaiian/Pacific Islander, 18% were Hispanic/Latino, 22% were mixed race, 35% were women, 4% identified as transgender, 1% as genderqueer/gender non-binary, and 1% as another gender. |
| Primary Objective | The primary objective is to assess feasibility and acceptability of:   - measuring biochemically-verified point prevalence abstinence at 6 months follow-up. - adhering to the protocol. - gathering information on the number of visits attended. - the retention protocol. |
| Secondary Objectives | - Assess feasibility and acceptability of measuring biochemically-verified 7-day point months follow-up at 3 months. - Assess feasibility and acceptability of measuring prolonged abstinence at 3 months and 6 months follow-up. - Assess feasibility and acceptability of measuring 12 point prevalence abstinence |
| Recruitment Methods | Recruitment methods include flyers, in-clinic recruitment, and via email to healthcare providers. |
| Sample Size | We plan to enroll 90 participants. |
| Duration of Study Participation | The intervention duration is 1 year. |
| Unique Aspects of this Study | This study will be the first to evaluate an extended contingency management intervention for smoking cessation for people experiencing homelessness. |

| List of Abbreviations *Add/Remove abbreviations as applicable to the study protocol* | |
| --- | --- |
| AE | adverse event |
| CRF | case report form |
| CTCAE | Common Terminology Criteria for Adverse Events |
| CTMS | Clinical Trial Management System |
| DSMC  DSMP | Data and Safety Monitoring Committee  Data and Safety Monitoring Plan |
| GCP | Good Clinical Practice |
| HDFCCC | Helen Diller Family Comprehensive Cancer Center |
| HIPAA | Health Insurance Portability and Accountability Act |
| ICF | informed consent form |
| ICH | International Conference on Harmonization |
| IRB  PHP | Institutional Review Board  Positive Health Program |
| PRC  RFPC  TWUHC  ZSFG | Protocol Review Committee (UCSF)  Richard H. Fine People’s Clinic  Tom Waddell Urban Health Clinic  Zuckerberg San Francisco General Hospital |

| Table of Contents |
| --- |


# Introduction

## Background

Cigarette smoking is exceedingly common among people experiencing homelessness, with a prevalence of 70% compared to 13.7% in the general population.^1,2^ Severe mental illness and substance use disorders are common among homeless adults and are risk factors for smoking and for poor smoking-related health outcomes.^3^ Smoking-induced cardiovascular diseases and cancers are the leading causes of morbidity and mortality among homeless adults.^4-8^

Homeless adults make quit attempts as frequently as the general population, but they are less successful at quitting completely.^9-11^ The quit ratio (former/ever smokers), a measure of successful quitting, among homeless adults is between 9% and 13%,^11,12^ almost 5 times lower than the general population (~61%).^2^ Clinical trials of behavioral counseling and pharmacotherapy—the standard care for smoking cessation—have failed to demonstrate substantial long-term abstinence among homeless adults.^13-17^ Long-term abstinence, defined as abstinence for 6 months or more, is a strong predictor of successful cessation.^18^ Behavioral counseling and pharmacotherapy alone may be insufficient to promote long-term abstinence, which is necessary to increase cessation rates among this population.

Cessation interventions not only need to be efficacious in clinical trials, but also scalable to practice settings.^19,20^ Although there have been randomized controlled trials (RCT) of cessation interventions for homeless adults, these trials have not been tested in practice-based settings. The majority of homeless adults in the U.S. seek health care in federally-funded, safety net community health centers. Safety net health clinics that provide care to homeless adults could bring cessation interventions to scale.

Research is needed to 1) identify interventions that can increase the effect of behavioral counseling and pharmacotherapy on long-term abstinence (≥6 months) among homeless adults; and 2) determine how such interventions can be brought to scale in safety net clinics serving homeless adults. As a step toward answering those questions, we will pilot test a RCT of a contingency management smoking cessation intervention for homeless adults seeking care in a safety net health clinic.

## Background on the intervention

Contingency management (CM), a behavior change strategy that reinforces positive health behaviors with incentives (e.g., cash), has been used in clinical trials to reduce tobacco and substance use in the general population.^21-24^ Smokers who abstain receive modest incentives; these incentives reinforce the healthy behavior.^21^ There have been clinical trials that have incorporated CM for the treatment of tobacco dependence among low-income pregnant women and persons with mental health or substance use disorders.^23,25-29^ Recent research, including uncontrolled pilot studies ^30,31^ and two recent pilot RCT,^32,33^ has demonstrated the feasibility of short-term CM (8 weeks or less) for smoking cessation among homeless adults. Some evidence suggests that extended CM, defined as CM for ≥12 weeks, can be efficacious in promoting long-term abstinence for ≥6 months.^21,34-39^ There are no feasibility trials evaluating extended CM to promote long-term abstinence among homeless adults, and none that have been adapted to safety net health clinics.

In this pilot randomized controlled trial (RCT), we will (1) adapt a known-efficacious extended CM cessation intervention to a novel population and setting, with the ultimate goal of increasing long-term abstinence among homeless adults seeking care in safety net health clinics, (2) develop a corresponding RCT protocol, and (3) conduct a pilot RCT to assess the feasibility and acceptability of the RCT. If the pilot RCT is feasible and acceptable, we will test the adapted intervention in a subsequently-funded, full-scale randomized controlled trial.

## Study Rationale

This study is being done to evaluate the feasibility and acceptability of an extended intervention for contingency management for smoking cessation for homeless adults. Some evidence suggests that extended CM, defined as CM ≥12 weeks (range 3 months to 1 year), among smokers with substance use disorders, can increase abstinence rates and efficacy of long-term abstinence for 6 months or more. In this pilot study, we will adapt a known-efficacious extended CM intervention, with provision of incentives for 6 months to promote abstinence for ≥ 6 months, to homeless adults engaged in care in a safety net health clinic.

## Risk/Benefit Assessment

**Potential risks.** There may be a potential for loss of privacy around homelessness status, which could affect participant’s standing in society. There may be a potential for loss of privacy relating to the information asked in the questionnaires, particularly around issues on mental health disorders, substance use disorders, and previous history of homelessness. Loss of privacy or confidentiality–particularly around mental health, illicit substance use, HIV status, impaired function, and information contained in medical records–could result in embarrassment or social marginalization. In the case of illicit substance use, loss of privacy or confidentiality could result in legal consequences. Because we will ask participants to consent to keep on file their name and contact and tracking information, there may be a potential for loss of confidentiality. Participants may experience symptoms of nicotine withdrawal from reducing consumption or quitting smoking. These symptoms may include irritability, fatigue, headaches or cravings for cigarettes. Participants may also experience hunger as a result of reducing consumption or quitting smoking. There is a possibility that participants may experience side effects from medications for cessation. There is a low risk of study participants experiencing fatigue and/or boredom during study visits. In addition to the above, we note other risks that may be relevant to our study population. Given the significantly low economic status of our study participants, study incentives and contingency management may be coercive. We believe that the risk of these events is low given the measures we will put in place to minimize these risks (see below).

**Procedures for protecting against risks.**

1. Procedures for protecting against loss of privacy. Although we collect basic information from homeless participants on socio-demographics and factors that can influence smoking cessation such as mental health disorders or substance use disorders, it will be kept to a minimum to minimize any psychological risk. All interviews will be conducted in a way that is formative without breaching the confidentiality of individuals participating in the study. We will ensure participants that responses to the questionnaires, in-depth, semi-structured interviews or focus groups will not affect their eligibility for receiving services. We will assure participants who decide not to participate that their decision would not affect their ability to seek services. Participation in this study is voluntary.
2. Procedures for protecting against loss of confidentiality. There is a potential for loss of confidentiality, however we will take measures to minimize this risk. Each participant will have a unique alpha-numeric identification (ID) number. We will use the UCSF REDCap secure database to enter personal identifying information and to create questionnaires for each of the studies. Identifying information collected from participants for tracking purposes will be stored separately from research data and will not be associated with the participants’ unique study ID number. All questionnaire data will be entered in real-time using an iPad through a secure VPN network. In-depth, semi-structured interviews and focus groups will be audio-recorded. These recordings and their transcriptions will be stored on our secure server at UCSF. The server where data will be stored is backed up nightly. We will periodically go through the study data to make sure there is no personal identifying information. Only study staff will have access to study data. For added protection of confidentiality, we will apply for Certificate of Confidentiality from the National Cancer Institute.
3. Procedures for protection against legal risk to participants. The structured interview will include questions about illegal behavior (e.g., the use of illicit drugs). Procedures explained above for protecting privacy of individuals and confidentiality of data will minimize the legal risk to participants. For added protection of confidentiality of data, we will apply for a Certificate of Confidentiality from the National Cancer Institute. Trained study staff will inform participants of legal risks during the informed consent process and will explain that participants can skip out of any interview questions they are not comfortable answering.
4. Procedures for protecting against coercion. Reimbursements may be coercive. There is controversy around whether reimbursements could be coercive or used to purchase illicit drugs when given to indigent populations participating in research. In trying to balance the need to reimburse participants for their time while limiting coercion and/or dangerous behaviors, we have set reimbursement levels comparable to those used in studies in similar populations.^18-20,22^ An alternative to cash reimbursements, we have chosen to reimburse in the form of gift certificates for grocery stores and general pharmacies.
5. Procedures for protecting against hunger. It is possible that individuals who are attempting to quit smoking may experience hunger. Should this issue arise during the intervention, we will provide clients a list of resources of free food around the city of San Francisco including food banks for food in bulk, soup kitchens for daily meals, and other free meal programs.
6. Procedures for protecting against withdrawal symptoms. Participants may experience symptoms of nicotine withdrawal from reducing consumption or quitting smoking. These symptoms include irritability, fatigue, headaches or cravings for cigarettes. We expect that participants enrolled in the clinical trial will be engaged in usual cessation care at the Tom Waddell Urban Health Clinic (TWUHC), The Richard H. Fine People’s Clinic (RFPC), or Positive Health Program Clinic (PHP), that includes one-on-one cessation counseling through behavioral counselors and NRT, dispensed on-site by a pharmacist, to prevent nicotine withdrawal and/or reduce cravings. Dosage of NRT will be adjusted according to participants’ consumption levels and based on participants’ urge to smoke. Primary care providers (PCPs) will verify and document in the EHR that there are no contraindications to receiving NRT such as having had a myocardial infarction in the 2 weeks prior to enrollment or pregnancy. HIPAA-trained study staff will access the EHR weekly to verify participants’ attendance of counseling and receipt of NRT. We anticipate that some participants may be co-prescribed varenicline or bupropion with NRT; we will document receipt of non-NRT medications by self-report at each visit and verify this information through the EHR. For participants who are unable to obtain medications, the study will provide a 12-week supply of NRT and study staff will discuss indications of use, contraindications, and potential side effects prior to use.
7. Procedures for protecting against adverse effects of cessation medications. PCPs will verify and document in the EHR that there are no contraindications to receiving NRT such as having had a myocardial infarction in the 2 weeks prior to enrollment or pregnancy. Participants who receive varenicline or bupropion from their PCPs will be asked to discuss the potential side effects with their PCPs before initiating medications, and study staff will confirm that this discussion has taken place. We will document receipt of non-NRT medications by self-report at each visit and verify this information through the EHR. At each assessment visit, study staff will assess adherence to medications and side effects of medications. We will ask participants to contact us in between visits if they experience side effects. If participants report side effects related to the use of cessation medications or if any psychiatric symptoms emerge, we will refer them to their PCPs. For serious concerns such as suicidal ideation or self-injurious behavior, we will refer them to the emergency room at the Zuckerberg San Francisco General Hospital, where the PI is an attending physician. The PI is a general internist with over 13 years of clinical experience, licensed in the state of California, and will be on call at all times to advise staff and can directly intervene with participants if needed.
8. Procedures for handling reportable conditions: During the informed consent process, participants will be informed of information that must be reported by law should it be revealed during study visits, including suicidality and homicidality. The PI will train the study staff on how to assess for symptoms of suicidality or homicidality, and the procedures to follow in the event of these occurrences. In addition, the PI will be on call at all times and will be available for consultation.
9. Procedures for protecting against fatigue or boredom: The enrollment study visit for the pilot RCT will last approximately 1 hour, and the follow-up visits at 2 weeks, 1 months, 3 months, 6 months, and 1 year will last approximately a half-hour. The in-depth, semi-structured interviews and focus group in Aims 1 and 2 will last 60 minutes to 90 minutes. Assessment visits for abstinence monitoring will last approximately 10 minutes. Regular breaks will be scheduled throughout the study visits, between structured interview instruments and assessments. Study staff will inform participants, during informed consent and at each study visit, that they can take breaks or stop participating in the study at any time.
10. Added protections for vulnerable populations: If a participant becomes incarcerated during the course of the study, they will be censored from participation during incarceration. If released from jail/prison during the study timeframe they can choose to re-enroll and a research assistant will repeat the informed consent process using procedures explained above.

**Risk benefit.** Given the minimal anticipated risks from this study, we think that proposed study has the potential to offer significant societal benefits. This study has the potential to inform development of an effective and scalable intervention to reduce tobacco use among homeless adults. In doing so, the study may inform future policies and interventions to reduce tobacco use and its associated morbidity and mortality among the diverse populations experiencing homelessness.

# Study Objectives and Endpoints

## Primary Objective

| **Primary Objective** | **Endpoint(s)** | **Time Frame** |
| --- | --- | --- |
| 1. Assess feasibility and acceptability of measuring biochemically-verified point prevalence abstinence at 6 months follow-up. | Evaluate the proportion of participants who achieve biochemically-verified 7-day point prevalence abstinence defined as participants (1) reporting not smoking a single cigarette in the past seven days, not even a puff; (2) having CO levels ≤5 ppm, and (3) anatabine/anabasine assays <2 ng/ml. | Baseline to 6 months follow-up |
| 1. Assess feasibility and acceptability of adhering to the protocol | Total number of carbon monoxide negative samples | Baseline to 6 months follow-up |
| 1. Assess feasibility and acceptability of gathering information on the number of visits attended | Total number of visits attended | 6 months |
| 1. Assess feasibility and acceptability of the retention protocol | Proportion of the sample retained as a result of retention procedures | 2 weeks, 1 month, 3 months, 6 months, and 12 months follow-up |

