**Clinical outcomes for the future full-scale RCT*.*** The primary outcome for the subsequent full-scale RCT will be biochemically-verified 7-day point prevalence abstinence at 6 months. Biochemically-verified 7-day point prevalence abstinence is defined as participants (1) reporting not smoking a single cigarette in the past seven days, not even a puff; (2) having CO levels ≤5 ppm, and (3) anatabine/anabasine assays <2 ng/ml. Secondary outcomes include 7-day point prevalence abstinence at 2 weeks and 3 months, and prolonged abstinence at each follow-up visit as per recent guidelines.^122^ We will also assess total number of CO-negative samples, longest duration of abstinence (i.e., total number of un-interrupted days of abstinence), total number of visits attended, and cigarette consumption for those unable to quit between the treatment groups. We will evaluate abstinence at 1 year to assess this outcome 6 months after incentives stop. In this pilot, we will assess the feasibility and acceptability of collecting each of these outcomes.

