## Adherence Assessment

Using a combination of qualitative and quantitative methods, we will evaluate whether: 1) we met our screening and recruitment goals, 2) the randomization scheme worked and that participants were willing to be randomized, 3) the CM intervention was delivered with fidelity, 4) the retention procedures enabled tracking and retention, 5) the outcome assessments were valid, reliable, and complete, and 6) participants adhered to the protocol (Table 2).

| **Table 2: Feasibility and acceptability outcomes** | | |
| --- | --- | --- |
| Outcomes | **Measure** | **Threshold** |
| Screening | # opting out, # screened | 40 screened per month |
| Recruitment | # enrolled per month | 8/month for 12 months |
| Randomization | Proportion enrolled who are randomized | 90% randomized to intervention and control arms^32^ |
| Fidelity | Observations of incentive payment delivery | Incentive payments that are due are delivered within 2 days of the visit by study staff |
| Adherence | Protocol adherence to the CO assessment schedule  Attendance to counseling sessions  Adherence to NRT among those prescribed NRT | 75% of those enrolled will provide a CO sample at 60%-70%, i.e., 14 -17 out of 25 possible assessment visits^32,33^  75% will attend at least 6 out of 12 counseling sessions during the treatment duration^33^  75% will adhere to using NRT for at least half of the treatment duration^33^ |
| Retention | Proportion of the sample retained as a result of retention procedures | 2 weeks (85%), 3-month (85%), 6-month (75%), and 1 year (75%) retention rates |
| Assessment | Proportion who completed all questionnaires | 75% completed all questionnaires |
| Acceptability | Questionnaire and qualitative interviews with staff and patients | 75% satisfied with the overall intervention |

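### Two primary feasibility objectives in Section 2.1 (protocol adherence and measurability of 6-month abstinence) are given abstinence counts as endpoints, in conflict with Table 2 and Section 9.3

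*Protocol*

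**What the plan says.** The endpoint table in Protocol Section 2.1 has four rows. Two are at issue.

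- Row 1. Objective: "Assess feasibility and acceptability of measuring biochemically-verified point prevalence abstinence at 6 months follow-up". Endpoint: "Evaluate the proportion of participants who achieve biochemically-verified 7-day point prevalence abstinence", with abstinence defined by self-report, CO and urinary anatabine/anabasine.
- Row 2. Objective: "Assess feasibility and acceptability of adhering to the protocol". Endpoint: "Total number of carbon monoxide negative samples", from baseline to 6 months.

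Rows 3 and 4 use the number of visits attended and the proportion retained.

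The Adherence Assessment section (Table 2) gives the feasibility measures and their thresholds. Its first adherence measure is "Protocol adherence to the CO assessment schedule", with the threshold "75% of those enrolled will provide a CO sample at 60%-70%, i.e., 14 -17 out of 25 possible assessment visits". Its assessment measure is "Proportion who completed all questionnaires", with a threshold of 75%. Its 6-month retention threshold is also 75%.

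Section 5.1, in the paragraph on clinical outcomes for the later full-scale trial, makes verified 6-month abstinence that trial's primary outcome. It then adds "We will also assess total number of CO-negative samples, longest duration of abstinence" among further outcomes, and says that the pilot looks at whether such outcomes can feasibly be collected.

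Section 9.3 compares each feasibility indicator with its tabled threshold. It handles the clinical outcomes separately, as descriptive statistics.

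**The concern.** A CO-negative sample requires two things: the participant attended and gave a sample, and the participant had not been smoking. Only the first is adherence to the assessment schedule. A missed visit and an attended visit with a positive reading both add nothing to the count, so the row 2 endpoint cannot separate poor attendance from continued smoking.

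Row 1 has a similar problem. Whether an outcome can be measured is a question about how many participants end up with a usable determination. The proportion abstinent is the value of that outcome, not its completeness.

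The pilot exists to decide whether to proceed to a full trial or first change the procedures. Its declared primary endpoints should therefore be the quantities on which that decision rests. As written, two of the four are not, and neither has a threshold in Table 2.

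**Working it through.** The protocol gives no power calculation or other figure to reproduce on this point. The check sets the passages side by side and adds simple arithmetic.

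**Inputs.** N = 90 (Section 3.2). Scheduled visits to week 24: 7 + 6 + 9 + 3 = 25 (Table 1), which agrees with the 25 in Table 2. A CO sample is due at every assessment visit (Section 3.1). The documents give no rates for samples provided or samples negative, so the rates below are assumptions for illustration.

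**One participant.** Attends 25 of 25 visits and smokes throughout:
- Section 2.1 row 2 (negative samples): 0.
- Table 2 adherence (samples provided): 25/25 = 100%.
- Section 2.1 row 3 (visits attended): 25.

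Another participant attends 10 visits, abstinent at each:
- Row 2: 10.
- Table 2: 10/25 = 40%.

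Row 2 ranks the second above the first. Table 2 ranks them the other way.

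**Whole trial.** Total negative = 90 × 25 × (share provided) × (share of those negative) = 2,250 × p × q.

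| Share provided p | Share negative q | Total CO-negative |
|---|---|---|
| 100% | 15% | 337.5 |
| 50% | 30% | 337.5 |
| 30% | 50% | 337.5 |

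The same total fits full, half and poor adherence. Conversely, with p fixed at 60% (15 of 25 visits), the total runs from 0 at q = 0% to 2,250 × 0.60 × 0.60 = 810 at q = 60%.

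**Row 1.** Suppose unmeasured participants stay in the denominator as not abstinent. The protocol states no such rule, so this is an assumption. Then:
- 100% measured, 5% of them abstinent: 90 × 1.00 × 0.05 = 4.5.
- 50% measured, 10% of them abstinent: 90 × 0.50 × 0.10 = 4.5.

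Both give 4.5/90 = 5%. If only measured participants were in the denominator, the proportion would carry no information on how many were measured. Either way, completeness cannot be read from it.

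**Is completeness covered elsewhere?** In Table 2, the adherence row counts CO samples over all 25 visits, the retention row sets 75% at 6 months, and the assessment row counts questionnaires. None counts participants who have the 6-month self-report, the 6-month CO and, where triggered, the urine result. At exactly the retention threshold, 0.25 × 90 = 22.5, so about 22 participants could lack a 6-month visit. Row 4 would show that loss, but no row shows a missing CO or urine result among those retained.

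The urine step can fail in a specific way. The text for Visits 24-26 triggers collection at CO below 5 ppm, while Section 2.1 accepts CO up to and including 5 ppm. A participant who reports abstinence with a reading of exactly 5 ppm meets the first two criteria, yet no urine is collected.

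**Thresholds.** Section 9.3 needs a tabled threshold for each indicator. Table 2 has none for CO-negative samples or for the proportion abstinent.

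**The case against.** The strongest reply is that the feasibility verdict does not rest on the two faulted endpoints. Section 9.3 ties it to Table 2, where adherence is correctly defined by samples provided, and the clinical outcomes are only described. Within Section 2.1, row 3 would credit the attending smoker with 25 visits, and row 4 would show loss by 6 months. All of this stands. It is why the point is a conflict in the stated endpoints and not a failure of the decision rule.

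Row 1 can also be read as merely naming the outcome whose collection is under study, which fits Section 5.1. That is probably the intent. The endpoint column nevertheless states the proportion abstinent, and no other indicator supplies the completeness measure.

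Three stronger readings are tempting and are not supported:

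- A reader might infer that a low CO-negative count would fail the 14-17 of 25 mark even with perfect attendance. That mark is for samples provided, and nothing in the protocol applies it to negative samples.
- A reader might infer that nothing in the plan bears on biochemical completeness. The adherence and retention rows do bear on it, and the Adherence Assessment section undertakes to look at whether outcome assessments were complete. What is missing is a numeric indicator specific to the 6-month determination.
- A reader might infer that the row 2 endpoint biases a comparison of the arms, because incentives for negative samples are paid in one arm only. The count may well differ by arm for that reason, but Section 9.3 proposes no inferential comparison and the Table 2 threshold applies to all enrolled.

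**Conclusion.** The point holds in a limited form. Two of the four primary endpoints in Section 2.1 measure abstinence where the objective is adherence or measurability. They conflict with Table 2, with the way Section 5.1 classes the same quantities, and with the threshold comparison in Section 9.3. Row 2 is the plainer contradiction, since Table 2 already holds a suitable measure. Row 1 leaves the larger gap, since no Table 2 row is specific to completeness of the 6-month self-report, CO and urine result.

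This conclusion needs no assumed rate. The contrast of 0 with 25 of 25 follows from the definitions, and the assumed rates only illustrate that the counts are not informative. The documents do not support the inference that the pilot would reach a wrong feasibility verdict on adherence. It should be fixed, but it is not a fatal defect.

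**What to change.** - **Section 2.1, row 2.** Make the endpoint the number and proportion of scheduled CO samples provided, whatever the result, judged against the Table 2 adherence threshold. State that threshold as one cut-off: 60%-70% of 25 is 15 to 17.5, whereas 14-17 of 25 is 56%-68%.
- **Section 2.1, row 1.** Make the endpoint the proportion of randomised participants with a complete 6-month determination: self-report and CO, plus a urine result where the first two criteria are met. Add it to Table 2 as an indicator and take its threshold from the existing 75% six-month retention figure. Reconcile the CO limit that triggers urine collection with the limit in the abstinence definition, so that the set needing a urine result is unambiguous.
- **Clinical outcomes.** Report CO-negative counts and the proportion abstinent descriptively, as Section 9.3 already foresees.
- **Section 2.2.** The secondary objectives also pair measuring with achieving abstinence, and the same wording change would serve there.

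The cost is a protocol wording amendment and one further tabulation from data already scheduled. No visits or samples are added, unless the urine trigger is aligned to include readings of exactly 5 ppm, which would add a urine sample for those participants.
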